# Efficacy and safety of fluzoparib combined with anlotinib in extensive stage small cell lung cancer after first-line platinum-based chemotherapy: a multi-center, single-arm prospective phase II clinical study (STAMP study)

**DOI:** 10.1186/s12885-023-11230-5

**Published:** 2023-08-14

**Keywords:** Fluzoparib, Anlotinib, Small cell lung cancer, Protocol

## Abstract

**Background:**

Small-cell lung cancer (SCLC) is a highly aggressive and lethal malignancy that accounts for 10–15% of lung cancers, and it is generally divided into limited and extensive stage. The standard of care for patients with newly diagnosed extensive-stage SCLC (ES-SCLC) is still platinum-based chemotherapy and as maintenance therapy scheme. Although most parts of patients experience a significant tumor response to first-line therapy, the disease recurs invariably. Anlotinib hydrochloride, a novel oral multitarget tyrosine kinase inhibitor, has significant inhibitory activity against angiogenesis-related kinases, such as VEGFR, FGFR, PDGFR, and c-Kit kinase associated with tumor cell proliferation. Fluzoparib is a type of inhibitor of poly ADP ribose polymerase (PARP, including PARPl, PARP2 and PARP3). Previous studies have shown that Fluzoparib has a strong inhibitory effect on PARP1 activity at the molecular and cellular levels.

**Methods:**

This is a multi-center, prospective, single-arm phase II clinical study. A total of 50 ES-SCLC patients who experienced disease progression after first-line standard platinum-based chemotherapy with/without immune checkpoint inhibitors scheme, or within 6 months after the completion of treatment will be recruited. Those who had prior treatment with any PARP inhibitor or antiangiogenic agent includes anlotinib, bevacizumab, sorafenib, and thalidomide are excluded. Eligible patients will receive oral anlotinib 8 mg once daily and oral fluzoparib 150 mg twice daily until disease progression or intolerable toxicity. The primary endpoint is objective response rate (ORR).

**Discussion:**

The addition of fluzoparib to anlotinib is expected to increase the clinical benefit in ES-SCLC patients after platinum-based chemotherapy.

**Trial registration:**

This study protocol was prospectively registered on June 17, 2021. ClinicalTrials.gov Identifier: NCT04933175.

## Background

In recent years, people have made large efforts in improving the existing maintenance treatment strategies for ES-SCLC patients after the standard first-line chemotherapy. The poor prognosis and no preferable options may be largely related to chemotherapy drug resistance. Non-activating mutations of *TP53* and *RB1* are the most common mutations in SCLC, regrettably, no definite target is confirmed to be useful till now. Newly diagnosed SCLC experience a significant tumor response to first-line platinum-based chemotherapy with a response rate of 50–70%. Sensitivity to platinum-based chemotherapy may be predicted via determining interval from the end of first-line chemotherapy to disease progression, and it is considered to be correlated with second-line chemotherapy efficacy. Overall, the response rate of second-line therapy for SCLC is low at 5–30% [1, 2].

Recently, targeting DNA damage repair therapy including PARP inhibitors have shown therapeutic efficacy in SCLC and is considered to be a new potential treatment strategy for SCLC [3]. Although homologous recombination deficiency (HRD) or *BRCA1/2* gene mutations was not detected in SCLC very often, PARP inhibitors showed some antitumor activity in some preclinical and early clinical studies. However, the tumor suppressive activity of PARP inhibitor alone in SCLC is relatively low. PFS of UK STOMP study using olaparib as a maintenance therapy after first-line treatment for SCLC failed to be improved [4]. Therefore, PARP inhibitors in combination with other antitumor agents are emerging as a new clinical research strategy. One phase I/II clinical study published in Cancer Discovery in 2019 enrolled 50 SCLC patients given olaparib 200 mg bid × 7d combined with temozolomide 75 mg/m2 QD × 7d Q3W after the failure of previous standard therapy, and the result presented an ORR of 41.7%, a median PFS of 4.2 months and a median OS of 8.5 months [5]. Tumor response was confirmed in olaparib in combination with PD-L1 monoclonal antibody durvalumab in second-line and beyond in SCLC, especially two of three patients with inflammatory phenotype achieved PR [6]. Based on the results of ALTER1202 [7], the CFDA approved anlotinib for third-line and beyond treatment of SCLC, and lots of clinical studies of anlotinib in combination with other antitumor drugs for second-line and beyond treatment of SCLC are conducted, including anlotinib combined with chemotherapy (ChiCTR1500030474, ChiCTR1900028430, ChiCTR1900021983, NCT03823118), anlotinib combined with immunotherapy (NCT04192682, NCT04055792, NCT04234607).

Preclinical studies showed that tumor vascular regression and tissue hypoxia caused by anti-angiogenic therapy increase the sensitivity of tumor cells to PARP inhibitors, suggesting a synergistic anti-tumor effect of PARP inhibiting and anti-angiogenic therapy [8, 9]. In addition, olaparib combined with Bevacizumab for solid tumors also showed anti-tumor activity in phase I clinical study with no serious adverse events related to olaparib or dose-limiting toxicities [10]. A phase II randomized placebo-controlled study of olaparib in combination with the pan-inhibitors of VEGFR cediranib for the second-line treatment of ovarian cancer showed a significant prolongation of median PFS compared to olaparib alone (17.7 months versus 9.0 months, HR = 2.9, *P* = 0.001) [11], which is suggested that combined therapy of PARP inhibitors and pan-inhibitors of VEGFR may have synergistic antitumor effect.

Anlotinib is also a pan-inhibitor of VEGFR, which also inhibits *PDGFR*, *FGFR*, c-*KIT* and other targets, and would have synergistic antitumor effect in combination with the PARP inhibitor fluzoparib theoretically. However, till now no clinical study on the combination of anlotinib and fluzoparib have been reported or registered. Pharmacokinetically, anlotinib is not the substrates of P-glycoprotein, mainly metabolized via CYP1A2 and CYP3A4/5, and mostly excreted in urine and feces. In terms of drug interactions, anlotinib has a moderate inhibitory effect on CYP3A, CYP2B6, CYP2C8, CYP2C9 and CYP2C19. Grade 3 or higher adverse reactions are mainly hypertension, hand-foot skin reaction and proteinuria. Fluzoparib is a substrate of the efflux transporter P-glycoprotein mainly metabolized via CYP3A4, and is mostly excreted as metabolites in urine and feces. In terms of drug interactions, fluzoparib has a relatively small effect on the inhibition of each CYP enzyme subtype and does not induce CYP3A4 or CYP1A2. The most common grade ≥ 3 treatment-emergent adverse events reported in the fuzuloparib group were anemia (25.1%), decreased platelet count (16.8%), and decreased neutrophil count (12.6%) [12]. The above pharmacokinetic studies showed metabolic transformation is the main pathway of anlotinib elimination, while renal excretion via urine was the main excretion route and fecal excretion was the secondary excretion route of fuzuloparib, therefore, the toxicity of the two drugs should not add up theoretically. In addition, real-world study data for a small number of patients treated with fluzoparib in combination with anrotinib showed no significant increase in toxic and side effects.

The combination of anlotinib and fluzoparib may theoretically decrease the metabolism of fluzoparib, increase its concentration in the blood and area in the drug curve. Therefore, fluzoparib dose should be reduced appropriately. Combination of anlotinib and fluzoparib would not make adverse events and not increase the incidence of ≥ grade 3 adverse events. In theory, it is feasible in combination of the anlotinib and fluzoparib.

The study protocol and informed consent of participant were discussed and approved by the Fujian Provincial Hospital Ethics Committee to fully protect the rights of participants, and the aim of the protocol is to explore the efficacy and safety of fluzoparib combined with anlotinib in the second-line treatment of patients with recurrent/extensive stage SCLC.

## Methods/design

### Study design

This is a multi-center, prospective, single-arm phase II clinical study (Fig. 1). A total of 50 ES-SCLC patients who have received standard platinum-based (two of cisplatin, carboplatin or lobaplatin) chemotherapy, and been considered to have disease progression assessed by imaging during the treatment period or within 6 months after the end of the last treatment according to RECIST1.1. will be recruited. The study is being conducted in accordance with the Declaratiion of Helsinki and Good Clinical Practice. The protocol and its amendments have been approved by local institutional review boards of all participating centers. The recruitment was started in May 2021.The enrolment is estimated to be completed in May 2022.

**Fig. 1 Fig1:**
[figure not shown]
Study design

### Eligibility criteria

The patient inclusion and exclusion criteria are detailed in Table 1.

**Table 1 Tab1:** Eligibility criteria

**Inclusion criteria**	Subjects who must meet all of the following inclusion criteria can be enrolled in this study
1	Be voluntarily enrolled in the study with signed informed consent, good compliance.
2	Age ≥ 18 years, age ≤ 75 years, regardless of gender.
3	Histologically and radiologically proved ES-SCLC according to the Veterans Adminstration Lung Study Group staging.
4	According to RECIST1.1 [13], at least one measurable lesion, and can be accurately measured at the baseline, the longest diameter of the baseline period ≥ 10 mm (in the case of lymph nodes, a short diameter ≥ 15 mm is required) without local treatment previously such as irradiation or tissue biopsy during the screening period. The selected measurement method is suitable for repeated measurement accurately, which can be computed tomography (CT) or magnetic resonance scan (MRI). If there is only one measurable suitable lesion, a baseline assessment of the tumor lesion should be performed at least 14 days after the diagnostic biopsy after acceptance as a target lesion.
5	Have received standard platinum-based (two of cisplatin, carboplatin or lobaplatin) chemotherapy, and been considered to have disease progression assessed by imaging during the treatment period or within 6 months after the end of the last treatment according to RECIST1.1.
6	The Eastern Cooperative Oncology Group (ECOG) physical status score of 0–2 with a minimum expected survival of 12 weeks.
7	Peripheral hemogram and liver and kidney function should achieve the following permissible limits (tested within 7 days prior to treatment initiation): White blood cells (WBC) ≥ 3.0 × 109/L or neutrophils (ANC) ≥ 1.5 × 109/L; (a) Hemoglobin (HGB) ≥ 80 g/L; (b) Platelets (PLT) ≥ 80 × 109/L; (c) Hepatic transaminases (AST, ALT) < 2.5 times the high limit of the normal range.; (d) Total bilirubin (TBIL) < 2 times the high limit of the normal range; (e) Creatinine (CREAT) < 1.5 times the high limit of the normal range.
8	Doppler ultrasound assessment: left ventricular ejection fraction (LVEF) ≥ low limit of normal (50%).
9	Women of childbearing age should take appropriate contraceptive measures from the beginning of screening to 3 months after stopping the treatment and should not breastfeed. No risk of pregnancy should be proved by a negative pregnancy test (urine or serum) within 7 days before the start of administration, or one of the following criteria a. Postmenopausal, defined as age ≥ 50, and amenorrhea for at least 12 months after cessation of all exogenous hormone replacement therapy. b. Postmenopausal age ≤ 50, and amenorrheic for 12 months or more after discontinuation of all exogenous hormone therapy, and luteinizing hormone (LH) and follicle-stimulating hormone (FSH) levels are within reference values for postmenopause. c. Previous irreversible sterilization, including hysterectomy, bilateral oophorectomy or bilateral salpingo-oophorectomy, not including bilateral tubal ligation.
10	Male patients should use barrier contraception (i.e., condoms) from beginning of screening to 3 months after stopping treatment.
11	Patients with asymptomatic brain metastases, or controlled brain metastases (clinical symptoms are stable for at least 2 weeks after symptomatic treatment for brain metastases). In addition, patients with prophylactic irradiation of the brain are allowed.
**Exclusion criteria**	Subjects are not eligible for enrollment in this study if they met any of the following criteria.
1	1. Have received any of the following treatments: a. Prior treatment with any PARP inhibitor or anti-angiogenic drug including anlotinib, avastin, sorafenib and thalidomide, etc. b. Have undergone major surgery within 4 weeks prior to the first dose. c. Have received more than 30% bone marrow irradiation or has received extensive radiotherapy within 4 weeks prior to the first dose.
2	Patients with uncontroled brainmets, or other malignant tumors, except basal cell carcinoma of the skin and carcinoma in situ.
3	The presence of significant cavitary lung tumors on imaging (CT or MRI).
4	Being treated in another clinical research study or having been treated in another clinical research study within 4 weeks prior to the start of the study.
5	Known hypersensitivity to the components of the study drug involved in the study.
6	Have received chemotherapy, radiotherapy or other experimental anticancer therapy (other than bisphosphonates) within 4 weeks prior to the first dose: those who have received prior local radiotherapy may be enrolled if the following conditions are met: the radiotherapy ended more than 4 weeks (more than 2 weeks for brain radiotherapy) from the start of study treatment; and the target lesion selected for this study is not in the radiotherapy area; or the target lesion is in the radiotherapy area but has been confirmed progression.
7	Patients who have not recovered from antineoplastic therapy-related adverse effects (except alopecia) to NCI-CTCAE ≤ grade 1 after prior systemic antineoplastic therapy.
8	Abnormal coagulation (INR > 1.5 or prothrombin time (PT) > ULN + 4 s or APTT > 1.5 ULN), with prone to bleeding or on thrombolytic or anticoagulant therapy; Note: The use of low-dose heparin for prophylactic purposes (adult daily dose of 0.6 to 1.2 10,000 U) or low-dose aspirin (dosage ≤ 100 mg daily) is accepted for prophylactic purposes.
9	Clinically significant hemoptysis (hemoptysis > ½ tablespoon per day) within 3 months prior to enrollment; or clinically significant hemorrhage symptom or prone to bleeding within 4 weeks prior to cohort, such as alimentary tract hemorrhage, hemorrhagic gastric ulcer (including gastrointestinal perforation and/or fistula, but the gastrointestinal perforation or fistula that has been surgically removed may be allowed), fecal occult blood (≥ + +) at baseline, unhealed wounds, ulcers, or fractures.
10	Renal insufficiency: urine protein ≥ + + , or 24-h urine protein amount > 1.0 g.
11	Patients with poor blood pressure control (systolic blood pressure ≥ 160 mmHg and diastolic blood pressure ≥ 100 mmHg) after drug therapy.
12	Patients with severe cardiovascular disease: grade II or higher myocardial ischemia or myocardial infarction, poorly controlled arrhythmias; grade III-IV cardiac insufficiency by NYHA criteria, or cardiac ultrasound suggestive of left ventricular ejection fraction (LVEF) < 50%.
13	The current presence of peripheral neuropathy ≥ CTCAE degree 2, except the cause of trauma.
14	Moderate or large uncontrolled plasma cavity effusions (including pleural, ascites, and pericardial effusions) via fluid aspiration, exacerbated chronic obstructive pulmonary disease, and respiratory disease in the active phase of pulmonary infection and/or acute bacterial or fungal infection that should accept intravenous antibiotic therapy.
15	There are factors that significantly affect absorption of oral drugs, such as inability to swallow, chronic diarrhea and intestinal obstruction.
16	Arterial/venous thrombotic events such as cerebrovascular accidents (including cerebral hemorrhage and cerebral infarction), deep vein thrombosis and pulmonary embolism that occurred within the 6 months prior to cohort.
17	Known history of psychotropic substance abuse, alcohol or drug abuse.
18	Active hepatitis (hepatitis B: HBsAg positive and HBV DNA ≥ 1 × 104 copies/ml; hepatitis C: HCV RNA positive and abnormal liver function) that cannot be controlled, or the combined infection of hepatitis B and C.
19	The positive blood or urine pregnancy result of women within 3 days prior to the first dose.
20	Poor compliance in the procedures and requirements of the study.
21	Any condition that will endanger patient's life or interference assessment results.

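### Inclusion criterion 7 sets no binding neutrophil minimum, because its white-cell limits are joined by *or*; the gap that remains is a low count not attributed to prior therapy

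*Protocol article*

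**What the plan says.** Table 1 of the protocol article requires every inclusion criterion to be met. Criterion 7 covers blood counts and liver and kidney function, "tested within 7 days prior to treatment initiation". Its white-cell item reads "White blood cells (WBC) ≥ 3.0 × 109/L or neutrophils (ANC) ≥ 1.5 × 109/L". Haemoglobin, platelets, transaminases, bilirubin and creatinine follow as items (a) to (e), each with its own limit. The white-cell pair is the only one offered as alternatives.

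Other parts of the article that bear on neutrophils:

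- Exclusion criterion 7 removes "Patients who have not recovered from antineoplastic therapy-related adverse effects (except alopecia) to NCI-CTCAE ≤ grade 1" after prior systemic treatment.
- Inclusion criterion 5 requires prior platinum-based chemotherapy for everyone.
- Exclusion criterion 6 requires a washout: "Have received chemotherapy, radiotherapy or other experimental anticancer therapy (other than bisphosphonates) within 4 weeks prior to the first dose".
- Exclusion criteria 1c, 2, 14 and 18 (marrow irradiation, other malignancy, active infection, active hepatitis) remove some other causes of a low count.
- Exclusion criterion 21 is a discretionary clause for conditions that endanger the patient or disturb assessment.
- The Background reports grade 3 or worse neutrophil decrease in 12.6% of patients on fluzoparib.
- Table 2 interrupts fluzoparib for grade 3 neutropenia.

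**The concern.** When two limits are joined by *or*, only the one that is easier to meet matters. A site that sees WBC at or above 3.0 × 10^9/L can tick criterion 7 without reference to the neutrophil count, so the ANC limit on the same line does no work for that patient.

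The neutrophil count is the safety-relevant number here. Fluzoparib lowers neutrophils. The Background also says that anlotinib may raise fluzoparib exposure, and that no clinical study of the combination had been reported or registered. Adverse events and dose adjustments due to adverse events are safety endpoints. With a single arm and no control, a low count present at entry could be recorded there as an effect of treatment. The stake is patient safety and clean safety reporting, not the efficacy comparison.

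**Working it through.** The plan has no figure of its own to reproduce. The check is a logical reading, one line of arithmetic, and a pass through the other criteria.

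**Inputs.** WBC limit 3.0 and ANC limit 1.5 (× 10^9/L), both from inclusion criterion 7. ANC = WBC × neutrophil share.

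**Step 1: when is the printed ANC limit bypassed?** A patient passes on WBC alone with ANC below 1.5 when the neutrophil share is below 1.5 / WBC:

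- WBC 3.0: 1.5 / 3.0 = 50.0%
- WBC 4.0: 1.5 / 4.0 = 37.5%
- WBC 5.0: 1.5 / 5.0 = 30.0%

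These use printed limits only. As an example, WBC 3.2 with 30% neutrophils gives ANC = 3.2 × 0.30 = 0.96, and the patient still meets inclusion criterion 7. The *or* also works the other way: ANC of at least 1.5 admits a patient with WBC below 3.0.

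**Step 2: could entry occur at a count for which Table 2 would hold fluzoparib?** The article prints no CTCAE cut-points, so the threshold is an assumption and is varied. The share below which a patient passes on WBC with ANC under the threshold is:

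| WBC | ANC threshold 1.0 (assumed for grade 3) | ANC threshold 0.5 (stricter assumption) |
|---|---|---|
| 3.0 | 33.3% | 16.7% |
| 4.0 | 25.0% | 12.5% |
| 5.0 | 20.0% | 10.0% |

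So inclusion criterion 7 alone would not stop it. These shares describe which patients the wording admits. They do not estimate how many there are.

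**Step 3: what do the other criteria stop?**

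- Exclusion 7 stops a low count above grade 1 if it is judged related to prior anticancer therapy. Since all patients have had platinum, this covers the likeliest cause, and grade 1 is a tighter bar than the grade 3 in step 2.
- Exclusion 6 gives counts four weeks to recover.
- Exclusion 1c ("Have received more than 30% bone marrow irradiation"), exclusion 2 ("other malignant tumors, except basal cell carcinoma of the skin and carcinoma in situ"), exclusion 14 ("acute bacterial or fungal infection that should accept intravenous antibiotic therapy") and exclusion 18 remove certain causes but set no limit on the count.
- Exclusion 21 depends on the investigator's judgement.

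**Result.** A patient reaches the gap only if WBC is at least 3.0, the neutrophil share is low, the site does not attribute the low count to prior therapy, none of the cause-specific exclusions applies, and the site does not invoke exclusion 21. In that case no numeric limit applies.

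**The case against.** The strongest objection is that exclusion criterion 7 already does the job. It bars therapy-related effects above grade 1, exempts only alopecia, and applies to a population in which everyone has had platinum. That largely stands. A reader might infer from the *or* that the trial has no neutrophil safeguard at all, or that grade 3 neutropenia after platinum could pass screening freely. The documents do not support either reading: a count attributed to prior chemotherapy is excluded at grade 2 or worse. What exclusion 7 does not supply is an objective limit. It works only once a site has decided on cause, and several centres make that decision separately.

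Three further objections are fair:

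- The 12.6% is a rate of events arising on treatment. It shows that the drug lowers neutrophils, but not how often patients would enter with a low count.
- Table 2 manages low counts once treatment has started, so harm is mitigated. It does not screen patients before the first dose.
- The *or* may be a slip of drafting or translation, and nothing shows that sites applied it literally. The article cannot settle this. If it is a slip, that is a reason to correct the wording.

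**Conclusion.** The point holds as a minor eligibility defect. Inclusion criterion 7 prints an ANC limit of 1.5 × 10^9/L that does not bind for any patient with WBC of at least 3.0 × 10^9/L, and no other criterion in Table 1 gives a neutrophil value. The exposed group is limited to patients whose low count is not attributed to prior therapy and is not caught by another exclusion. Its size cannot be derived from the article and is probably small.

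The bypass shares of 50%, 37.5% and 30% rest on printed limits alone. Any statement about entry at grade 3 rests on an assumed cut-point and, given exclusion 7, applies only to neutropenia not attributed to prior therapy. The response rate endpoint, sample size and analysis do not change.

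**What to change.** In inclusion criterion 7, replace *or* with *and*, so that WBC of at least 3.0 × 10^9/L and ANC of at least 1.5 × 10^9/L are both required. At minimum, require ANC of at least 1.5 × 10^9/L for every patient.

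The edit is one word. A peripheral blood count is already required within 7 days before treatment, so no extra visit or sample should be needed, provided the neutrophil count is recorded for every patient. The costs are possibly a few fewer eligible patients and an amendment through the review boards of the participating centres. The change sets a floor at screening only; a result up to 7 days old does not guarantee the count at the first dose.

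The article expected enrolment to finish in May 2022, before its publication in August 2023. If enrolment has closed, the useful step is to state which rule the sites applied and to report baseline ANC alongside the haematological safety results.

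### Exclusion criterion 8 ties the clotting-test limits to a second condition, so read literally an isolated INR, PT or APTT abnormality does not exclude a patient

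*Protocol article*

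**What the plan says.** All places are in the protocol article, Table 1 (Eligibility criteria), unless stated.

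- **Exclusion 8** opens with abnormal coagulation, defined by INR above 1.5, PT above ULN + 4 s or APTT above 1.5 ULN. After a comma it adds "with prone to bleeding or on thrombolytic or anticoagulant therapy". A Note then allows prophylactic low-dose heparin and says that "low-dose aspirin (dosage ≤ 100 mg daily) is accepted for prophylactic purposes".
- **Exclusion 9** separately excludes "clinically significant hemorrhage symptom or prone to bleeding within 4 weeks prior to cohort". It gives no INR, PT or APTT limit.
- **Exclusion 10** joins two alternative grounds by *or*: a dipstick result, "or 24-h urine protein amount" above a limit.
- **Inclusion 7** begins "Peripheral hemogram and liver and kidney function should achieve the following permissible limits". It lists blood counts, transaminases, bilirubin and creatinine, but no clotting test.
- **Exclusion 21** is a general clause: "Any condition that will endanger patient's life or interference assessment results".
- **Table 2 (Dose adjustment criteria), anlotinib**: bleeding or coagulation abnormalities of grade 2 interrupt the drug and lower its dose. Grade 3 or above, or a second occurrence at grade 2 or above, means withdrawal.

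**The concern.** Exclusion 8 is a bleeding-safety screen before treatment with an anti-angiogenic drug. Three numeric limits are spelled out, yet the word *with* makes them conditional on a bleeding tendency or on treatment. A site that applies the criterion as written would admit a patient whose only finding is a clotting test above the stated limit. Another site, applying what the criterion seems to mean, would exclude the same patient, and this is a multi-centre study. Table 2 treats coagulation abnormalities during treatment as a reason to interrupt or withdraw anlotinib, so the entry rule should be at least as clear. What is at stake is patient safety and consistent screening, not the efficacy analysis.

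**Working it through.** The plan gives no figure to reproduce. The check is one of logic and of cover by other criteria.

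**Step 1: the possible readings of exclusion 8.** Let L = at least one clotting test above its limit, B = bleeding tendency, T = thrombolytic or anticoagulant therapy.

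- Reading 1: L and (B or T)
- Reading 2: (L and B) or T
- Reading 3: L or B or T, which requires taking *with* as a slip for *or*

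**Step 2: an isolated test abnormality.** Take an assumed patient with INR 2.0 (above 1.5), no bleeding tendency and no such therapy: L = yes, B = no, T = no.

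| Reading | Evaluation | Result under exclusion 8 |
|---|---|---|
| 1 | yes and (no or no) | not excluded |
| 2 | (yes and no) or no | not excluded |
| 3 | yes or no or no | excluded |

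Both readings that keep the printed word admit this patient. Only the reading that changes it excludes.

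**Step 3: does another criterion catch the patient?**

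- Inclusion 7: no clotting test among its limits.
- Exclusion 7: bars only adverse effects of earlier anticancer therapy that have not settled to grade 1 or below. It gives partial cover, for treatment-related abnormalities.
- Exclusion 9: needs bleeding symptoms or tendency; this patient has neither.
- Exclusion 12: concerns cardiac disease, including "poorly controlled arrhythmias"; no clotting limit.
- Exclusion 16: concerns past events such as "deep vein thrombosis and pulmonary embolism that occurred within the 6 months prior to cohort"; no clotting limit.
- Exclusion 21: judgement only, with no threshold.

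So no explicit limit elsewhere excludes the patient.

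**Step 4: what the thresholds do under each reading.** Exclusion 9 already removes recent bleeding tendency whatever the test results.

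- Under reading 2, the combination L and B adds almost nobody whom exclusion 9 does not already remove.
- Under reading 1, the thresholds matter mainly for patients already on therapy.
- Only under reading 3 do they have a function of their own.

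Together with the use of *or* between grounds in exclusion 10, this points to reading 3 as the intent. The printed wording therefore departs from the evident purpose.

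**Step 5: therapy with tests within limits.** Here L = no, B = no, T = yes. Reading 1 gives no and (no or yes) = not excluded. Reading 2 gives (no and no) or yes = excluded. Reading 3 gives no or no or yes = excluded. The Note makes its exceptions by drug and dose and does not mention test results. That is the form of an exception to a drug-based exclusion, and it fits readings 2 and 3, not reading 1.

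**Step 6: size.** One patient of the planned 50 is 1/50 = 2%. This is the weight of any single patient, not an estimate of how many would be affected.

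**The case against.** The strongest reply is that context already settles the meaning. The thresholds make sense only as a ground of their own, the English of the table is loose throughout, and a clinician would probably treat an INR above 1.5 as the abnormality to be excluded. Exclusion 7 and the liver limits in inclusion 7 also remove some patients with deranged clotting, an investigator must still be satisfied under exclusion 21, and Table 2 manages events during treatment. The article may condense a full protocol with better wording.

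Much of this stands. The intent is probably clear, the remaining group is narrow, and no frequency is given. But partial cover is not a clotting limit, and rules for managing events after dosing do not replace screening before it. The article says that the criteria are detailed in Table 1, so the fault lies in what is stated there, not in something left out. A probable intent still needs correct wording.

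A reader might go further and infer that the plan leaves open whether therapeutic anticoagulation with normal tests excludes, for instance in a patient treated for a thrombosis older than the 6 months in exclusion 16, or for a controlled arrhythmia outside exclusion 12. The documents do not support giving that equal weight. The Note exempts only low-dose prophylactic heparin and low-dose aspirin, which implies that therapeutic anticoagulation is itself a ground for exclusion.

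**Conclusion.** The point holds as a minor error in the wording of a safety rule. As printed, exclusion 8 does not exclude an isolated INR, PT or APTT abnormality, and no other explicit criterion does so. The treatment of therapeutic anticoagulation is implied by the Note and needs only to be stated.

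The conclusion rests on the literal sense of *with* and on the inference, from exclusions 9 and 10 and the Note, that separate grounds were meant. The INR of 2.0 is illustrative. The number of patients affected is unknown; that it is small is a judgement. It would be wrong to infer a deliberate decision to admit such patients, or any effect on the primary endpoint, sample size or power: nothing in the article supports either.

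**What to change.** Replace *with* by *or* and set out the criterion as separate grounds, each sufficient alone:

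- (a) INR above 1.5, PT above ULN + 4 s or APTT above 1.5 ULN;
- (b) bleeding tendency, with a cross-reference to exclusion 9;
- (c) thrombolytic or therapeutic-dose anticoagulant treatment, with the Note's exception for low-dose heparin and low-dose aspirin attached to (c) only.

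The cost is one reworded criterion, and a few patients with isolated abnormal tests become ineligible. The article expected enrolment to end in May 2022. If it has ended, the sponsor can still correct the text and state which reading the sites applied.
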